**4. What is your plan for primary variable analysis?**

***Analysis between weight loss, insulin sensitivity and immune health:***

Data will be analyzed using R (Vienna, Austria, 2011). A two-way repeated measures analysis of variance (ANOVA) will be used to assess time course differences (group x test) for **AIM 1** and **AIM 2**. A repeated measures ANOVA will also be used to assess differences in adipose cell depot among groups (**AIM 3**). Bonferonni post-hoc analysis will be used to determine group differences and paired t-tests will be used to assess within treatment effects. Linear regression analyses will be used to identify relationships between respective variables. A *P*<0.05 will be considered statistically significant. Data will be expressed as mean ± SEM.

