
# Hypothesis to be Tested

The central hypothesis is that pre-operative metabolic health is an important predictor of bariatric surgery effectiveness. We hypothesize that there is an adipose-derived immunosignature that predicts post-operative recurrence of obesity related CVD abnormalities and that targeting reductions in obesity BEFORE surgery will enhance the success of bariatric surgery on this disease risk. We expect that the combination of exercise and diet will be more successful at improving insulin sensitivity and reducing immune cell dysfunction compared to diet alone as well as expect that exercise will be superior to standard of care alone. These separate studies are expected to provide unique insight to the mechanism by which diet and/or exercise impact immune metabolism in obese patients, and this will shape the development of future studies in bariatric patients per se.

Primary Objectives:

1. **Ascertain the effects of Ex+CR vs. CR in obese subjects and Ex vs. standard of care (SC, i.e. control) BEFORE surgery on cardiometabolic risk.**
2. **Examine the effects of Ex+CR vs. CR in obese subjects and Ex vs. standard of care (SC, i.e. control) BEFORE surgery on surgical complications and quality of life.**
3. **Determine if circulating immunophenotyping after Ex+CR vs. Ex vs. CR vs. SC correlate with immune composition of adipose cell depots (omental and subcutaneous) at the time of surgery or post-intervention testing**.

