**2. What are the statistical considerations for the protocol?**

This study is a between-within subjects repeated measures design in which insulin sensitivity will be measured before and after interventions across 4 experimental conditions. The outcome measures to be assessed are as follows:

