**Outcome assessments pertaining to the primary objective:**

- 1. Assess the absolute mean difference in the 3-hr postprandial glucose AUC between the 2 different conditions undergoing bariatric surgery and the 2 different groups not undergoing bariatric surgery.
  2. Assess the absolute mean difference in the 3-hr postprandial insulin AUC between the 2 different groups undergoing bariatric surgery and the 2 different groups not undergoing bariatric surgery.
  3. Compare the postprandial insulin sensitivity across conditions (as measured by the insulin sensitivity index- ISI; a calculated value based on the glucose/insulin values obtained from the MMTT or OGTT)
  4. Compare the mean change in body fat between groups.
  5. Compare the mean change in body weight between groups.
  6. Assess the change in cardiorespiratory fitness between groups.
  7. Determine and compare the immunophenotype from blood between groups.
  8. Relate the insulin sensitivity responses to the immunophenotyping from blood via correlations.
  9. Relate the pulse wave velocity responses to the insulin sensitivity and immunophenotyping under each condition by calculating a 3-hour pulse wave velocity AUC.
  10. Relate the augmentation index responses to the insulin sensitivity and immunophenotyping under each condition by calculating a 3-hour pulse wave velocity AUC.

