**B. Treadmill or cycle ergometer exercise testing for cardiovascular fitness (i.e. VO2max)**:

- Subjects will be asked to perform a maximal treadmill or cycle ergometer exercise test in the Exercise Physiology Core Laboratory in the School of Medicine. The treadmill test will begin with low speed on the treadmill, and the speed and/or elevation will increase gradually every 2 minutes. You will complete the treadmill test if undergoing bariatric surgery. However, if you are not undergoing bariatric surgery, then you will perform the cycle ergometer test. The cycle ergometer test will begin with low resistance on the bicycle wheel, and the resistance will increase gradually every 3 minutes. Subjects will be asked to go as long as they can, that is, until they feel exhausted.
- During the test, subjects will have continuous electrocardiogram (ECG) heart monitoring and blood pressure monitoring by professionally qualified exercise physiologists of the Exercise Physiology Core Lab. All testing procedures follow the American College of Sports Medicine Guidelines.
- During exercise testing researchers will also measure the subjects’ metabolic rate, a measure of the amount of energy it takes to burn calories. During exercise subjects will wear a facemask that is connected to a special device (metabolic cart) that measures subjects’ exhaled carbon dioxide (CO_2_) and oxygen. These measurements are then used to calculate the amount of calories they burn.
- During the exercise test, the subject will wear a mask over their nose and mouth. This allows the researchers to measure how much oxygen the subject is using and will tell the researchers what the subject’s fitness level is.
- The visit ends after the subject completes the exercise test. The subject will receive the results of their test after the completion of the study.
- Subjects will also be provided with an **accelerometer** and instructions on how to use the accelerometer. The accelerometer is a small device, similar to a pedometer, which is worn on the belt and records the amount of activity performed. Data will be downloaded from it on a weekly basis.

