**Blood draws**:

- In the morning of the 4 study testing days, an IV catheter will be inserted into a vein in either the forearm or the back of the subject’s non-writing hand.
- The IV catheter will be in their arm for the remainder of each visit (about 5 hours), and removed before they leave the CRU.
- During the 4 study visits their blood will be drawn as follows:
  - Fasted
  - Every 30 minutes up to 180 minutes after their drink the beverage
- On each visit, a total of approximately 5-6 tablespoons of blood will be drawn. The blood we take will be tested to measure glucose, insulin, and substances that will help estimate blood glucose control and vessel health.
- A sweet mixed-meal that contains 4 oz of boost meal shake will start the mixed-meal tolerance test (MMTT) for bariatric patients. An oral glucose tolerance test (OGTT) will be given to subjects not undergoing bariatric surgery.
- Non-bariatric patients will have blood drawn (6 ml per draw; 2 draws) to assess blood microparticles, a new biomarker to assess cardiovascular disease risk, at visit 3 and visit 6 (or 18).
- Once the subject drinks the glucose beverage they will return to bed for the remaining blood draws (3-hours)
- When the blood draws are completed they will be fed lunch and discharged to go home.

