***Phase 4: Interventions***

Prior to the intervention subject’s undergoing bariatric surgery will be match paired to receive either standard medical care (SC) or exercise + standard care for 4 weeks. Subject’s not undergoing bariatric surgery will then be randomized to the exercise + diet + standard care group or diet + standard care group for 2 weeks.

*Standard medical care:* If subjects are assigned to this group they will not be provided materials to consume healthy diet and increase exercise participation. Subjects will also be asked to participate in the standard education sessions that are provided to all bariatric surgery patients. This standard care includes meetings with a nutritionist, a psychologist, and a bariatric surgeon.

*Diet + standard medical care*: If subject’s are assigned to this group they will be instructed to follow a weight loss diet plan, created for them by the research team. The diet will restrict your caloric intake to 1000-1400 calories per day. Subject’s will be given two meal replacement shakes each day and advice for preparing a standard, calorie-limited dinner designed for weight loss. Subjects are required to pick up food at least 1 time a week. Subjects will return empty bottles of meal shakes to confirm compliance.

*Exercise training* + *standard medical care for bariatric patients*: If subject’s are assigned to this group they will participate in exercise training and the standard medical care outlined above. Subject’s will be asked to exercise 5 days/week. Subject’s will be able to attend regularly supervised and scheduled training sessions with the exercise physiology staff members in Memorial Gym or they can exercise on their own. Overall, the training program will ask subject’s to exercise 5 times per week and 30 min/day. Subject’s heart rate will be monitored continuously during all training sessions, and they will be asked to exercise at an intensity 65-85% of their previously measured HRmax. Walking will be the main type of exercise. In addition to this training program, subject’s will participate in the standard education sessions that are provided to all bariatric surgery patients.

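### The group-by-test ANOVA for Aims 1 and 2 does not separate the surgical and non-surgical cohorts, so any cross-cohort comparison confounds treatment with cohort

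*Protocol*

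**What the plan says.** Protocol, Statistical Considerations, item 2, treats the study as one between-within repeated measures design in which "insulin sensitivity will be measured before and after interventions across 4 experimental conditions". The third outcome under the primary objective is to "Compare the postprandial insulin sensitivity across conditions", with the index taken from whichever challenge test the subject had. Item 4 gives the model for Aims 1 and 2: "A two-way repeated measures analysis of variance (ANOVA) will be used to assess time course differences (group x test) for" those aims. It adds that Bonferroni "post-hoc analysis will be used to determine group differences and paired t-tests will be used to assess within treatment effects". Item 5 carries the same approach over to the secondary variables. None of these places separates the cohorts, names a planned contrast or gives the number of Bonferroni comparisons.

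Elsewhere the protocol describes two cohorts handled differently. Under Blood draws, bariatric patients have a mixed-meal test, whereas "An oral glucose tolerance test (OGTT) will be given to subjects not undergoing bariatric surgery". For fitness, bariatric patients use the treadmill, but "if you are not undergoing bariatric surgery, then you will perform the cycle ergometer test". Phase 4 gives the surgical arms 4 weeks, and gives the other cohort the exercise-plus-diet group or the "diet + standard care group for 2 weeks".

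The first primary objective is narrower than the model: "Ascertain the effects of Ex+CR vs. CR in obese subjects and Ex vs. standard of care (SC, i.e. control) BEFORE surgery on cardiometabolic risk". Objective 2 uses the same two comparisons.

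**The concern.** Each of the features that separates the cohorts is constant within a cohort. A contrast such as Ex+CR vs Ex therefore mixes the effect of adding diet with surgical status, allocation method and treatment length. For some outcomes it also mixes in a different stimulus or ergometer. No covariate can separate these factors.

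Two things are at stake. A reader could take a cross-cohort p-value as an intervention effect. And if the Bonferroni family includes the cross-cohort pairs, the two comparisons that objectives 1 and 2 ask for lose power in a study with few completers.

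**Working it through.** **1. The cohorts side by side** (Study Design; exercise testing; Blood draws; Phase 4; the two visit schedules)

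| | SC, Ex | CR, Ex+CR |
|---|---|---|
| Population | surgical | non-surgical |
| Allocation | match-paired | randomized |
| Duration | 4 weeks | 2 weeks |
| Challenge test | MMTT | OGTT |
| Fitness test | treadmill | cycle |

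The Brief Summary and Statistical Considerations item 1 describe allocation differently (all subjects matched, no randomization). The table follows Study Design, Phase 4 and the schedules.

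**2. Contrasts.** Four groups give 4 × 3 / 2 = 6 pairs. Pairs with one arm from each cohort number 2 × 2 = 4. That leaves 2 within-cohort pairs, the two in objectives 1 and 2.

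**3. Which outcomes are affected, and how.** Glucose and insulin AUC, ISI and VO2peak come from a different test in each cohort, so there the measurement differs as well. Weight, body fat and blood immunophenotype have no cohort-specific method. For them the confounding is by population, allocation and duration only.

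**4. The plan's own sample sizes.** The justification gives 5, 6 and 10. A two-sided paired t-test at alpha 0.05 and 80% power gives 5.05 (2/1.2), 5.28 (2.4/1.5) and 9.94 (3.1/3.1), which matches those figures to rounding. They use an unadjusted alpha of 0.05, so nothing is allowed for Bonferroni.

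**5. Power for Ex+CR vs CR.** Inputs:
- Effect: 3.1 kg / 3.1 kg = 1 SD, from the sample-size justification, used here as a yardstick.
- Completers: 24 non-bariatric (Human Participants, item 2), or 12 per group if split equally.
- Pooled df, if all four groups share an error term: 24 + 12 − 4 = 32.

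Power is the probability that a noncentral t with noncentrality d√(n/2) exceeds the critical value. With d = 1 and n = 12, the noncentrality is √6 = 2.449.

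| Family | Alpha | df | Critical t | Power |
|---|---|---|---|---|
| one contrast | 0.05 | 22 | 2.074 | 0.649 |
| two contrasts | 0.025 | 22 | 2.405 | 0.527 |
| six pairs | 0.00833 | 22 | 2.899 | 0.352 |
| six pairs | 0.00833 | 32 | 2.812 | 0.374 |

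The 80%-power detectable difference is 1.20 SD in the first row and 1.50 SD in the last. With all 14 per group retained, power is 0.72, 0.61 and 0.43 at the three alphas (own-cohort df).

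**6. Ex vs SC.** There are 12 bariatric completers, so 6 per group. By the same formula, the detectable difference at 80% power is 1.80 SD for a separate unpaired test at 0.05 (df 10, critical t 2.228). Under six-way Bonferroni with pooled df it is 2.13 SD (df 32, critical t 2.812). Pairing is ignored in both, because the protocol gives no within-pair correlation.

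**The case against.** The strongest reply is that the item 4 sentence says neither one model nor four groups. Objectives 1 and 2 name within-cohort contrasts, the hypothesis section speaks of separate studies, and the cohorts are sized and scheduled separately. The first two primary outcomes can also be read within cohort. This stands in part: the pooled analysis comes from reading item 4 together with the four-condition design in item 2 and the cross-condition ISI comparison. Those two statements do not fit a purely within-cohort reading, and nothing in the protocol overrides them.

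Several stronger readings are tempting but not supported.

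- **That the plan imposes a six-way Bonferroni correction.** The family is not stated. Six is the all-pairs default for four groups, two is equally possible, and separate analyses would carry no penalty. Fixing the family can also be left to an SAP.
- **That the primary objectives need only two contrasts.** This is true of objectives 1 and 2. Objective 3 is worded across all four arms, and item 4 gives Aim 3 an analysis among groups.
- **That every outcome pools unlike assays.** Only the challenge-test outcomes and VO2peak do.
- **That the missing post-surgery test breaks the primary ANOVA.** Objectives 1 and 2 concern effects before surgery, and all four groups have the pre and post-intervention tests. The 1-month response is a secondary outcome.
- **That the 2.1 SD figure for Ex vs SC measures the Bonferroni cost.** The comparator is 1.80 SD, so most of it reflects 6 subjects per group.

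The protocol also calls its data preliminary. That limits what rides on any p-value, but does not make a confounded contrast interpretable.

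**Conclusion.** The concern holds in limited form. As written, the plan calls for comparing insulin sensitivity across four conditions that belong to two non-comparable cohorts, with no instruction to analyse them apart. Any of the four cross-cohort contrasts confounds treatment with cohort. This conclusion rests on the text alone.

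The power cost is conditional. At 12 per group and a 1-SD effect it ranges from none (65%, separate tests) through 53% to 35–37%, depending on the unstated family. For Ex vs SC at 6 per group, the detectable difference moves from 1.80 to about 2.1 SD in the six-pair case. These figures assume equal splits of the stated completers and unpaired tests.

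**What to change.** - For Aims 1 and 2, specify two within-cohort group-by-test analyses over the pre and post-intervention tests, each with one planned contrast: Ex vs SC, accounting for the matched pairs, and Ex+CR vs CR.
- State whether the two contrasts are each tested at 0.05 or adjusted together at 0.025.
- Analyse the 1-month post-surgery test in the bariatric cohort only, as a secondary analysis.
- Remove cross-cohort testing of glucose and insulin AUC, ISI and VO2peak, and show other cross-cohort results descriptively.
- For objective 3, stratify or adjust the correlations and the adipose depot comparisons by cohort.

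No new subjects, visits or assays are needed. The sponsor gives up cross-cohort p-values, and must amend the four-way wording of objective 3 and the Aim 3 analysis among groups to match. Ex vs SC also loses the pooled error degrees of freedom. Even so, its detectable difference under the separate unpaired test (1.80 SD) is smaller than under the six-pair pooled analysis (2.13 SD).

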# Brief Summary/Abstract

Obesity is a major health concern that has been associated with an estimated 2.8 million deaths worldwide each year. The number of individuals considered obese with a Body Mass Index (BMI) above 30 kg/m^2^ has grown to more than 500 million. The increased morbidity and mortality associated with obesity stems from a long list of comorbidities, including hypertension, coronary artery disease, stroke, cancer, and type 2 diabetes (T2D). Bariatric surgery is an emerging intervention that has been used frequently to induce weight loss for obese individuals and it has been shown to improve glycemic control and insulin resistance in people at risk for type 2 diabetes. Beyond weight loss and improved glycemic control, surgery may lead to healthy improvements in inflammation, immune cells and vascular health. It is already known that exercise and weight loss from lifestyle modification can improve glycemic control, insulin resistance, levels of inflammatory cytokines, gut bacteria and arterial stiffness. However, no work has been done to examine a combination of bariatric surgery and pre-surgery lifestyle modification with diet and exercise. Recent work by our team has evidence demonstrating that health status pre-surgery has an impact on post-surgery outcomes. Such findings suggest that improvements in health status from exercise and/or caloric restriction before surgery may improve surgery outcomes as well as surgery-induced health outcomes. To date, no study has systematically examined the role of diet and/or exercise on the prevalence of surgery complications or on post-surgery weight loss, glycemic control, and insulin resistance. Moreover, no work currently exists with lifestyle modification, with or without bariatric surgery on adipose tissue derived inflammation related to immune cells or gut bacteria. Therefore, the purpose of this study is to investigate the effect of pre-surgery lifestyle intervention with diet and/or exercise on bariatric surgery outcomes. To test this objective, subjects will participate in a match paired study, based on BMI. Subjects will undergo testing of blood chemistry and related measures of health before and after lifestyle intervention, as well as 4 weeks post-bariatric surgery. The subjects will be match paired to standard care or exercise until these interventions are filled. Once standard care and exercise interventions are full subjects will then be match paired to exercise plus diet and then diet last. After the intervention all subjects will receive surgery. Post surgery outcomes will be assessed by examining surgery operating time, changes in blood chemistry, adipose tissue biopsies and other measures indicative of glucose and vascular health.

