**►IF YES, explain the kind of controls to be used.**

Subjects will have pre-intervention testing to determine efficacy of exercise and/or diet on insulin sensitivity and immune health.

1. **What is the study design?**

Matched pair, prospective design. Bariatric patients will be match paired to the exercise or standard medical care group. Subjects not undergoing bariatric surgery will be randomized to calorie restriction or calorie restriction + exercise groups.

1. **Does the study involve a placebo?**

No

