##### 4. How many subjects will sign a consent form under this UVa protocol?

A total of 60 subjects will sign the consent form.

1. **Provide an estimated time line for the study.**

We anticipate this study will take approximately 18-36 months to meet 100% enrollment. Each participant will be enrolled for a total of approximately 12 weeks from the time of screening to study completion. Our team will interact with 4-5 subjects at one time. As a result, approximately 8-12 subjects per year will be enrolled.

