# Statistical Considerations

1. **Is stratification/randomization involved?**

No. Subjects will be match paired.

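### The bariatric exercise and standard-care arms are formed by match pairing, but the stated analysis has no BMI or pair term; where BMI relates to the outcome, the comparison is conservative and loses precision

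*Protocol*

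**What the plan says.** **Design.** The Brief Summary states that "subjects will participate in a match paired study, based on BMI". The study-design answer reads "Matched pair, prospective design. Bariatric patients will be match paired to the exercise or standard medical care group". Asked whether stratification or randomisation is involved, Statistical Considerations item 1 answers "No. Subjects will be match paired". The Interventions section and the bariatric visit schedule repeat match pairing for these arms. Only the Brief Summary names BMI as the matching variable.

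**Contrast.** The first primary objective includes "Ex vs. standard of care (SC, i.e. control) BEFORE surgery on cardiometabolic risk".

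**Analysis.** Item 2 of Statistical Considerations describes the model: "This study is a between-within subjects repeated measures design in which insulin sensitivity will be measured before and after interventions across 4 experimental conditions". Item 4 fixes the test: "A two-way repeated measures analysis of variance (ANOVA) will be used to assess time course differences (group x test"), for Aims 1 and 2. It adds a repeated measures ANOVA for adipose depots (Aim 3), Bonferroni post-hoc comparisons and linear regressions. Its only paired tests are t-tests for change within a treatment, that is, the same subject before and after. Item 5 applies the same approach to the secondary variables. Neither BMI nor the pair enters any of these models.

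**The concern.** Allocation to Ex or SC is not randomised, so matching is the only stated means of making the two bariatric arms comparable. The analysis then ignores it. If matched partners have correlated outcomes, the variance of the arm difference is smaller than an independent-groups test assumes, and that test reports too large a standard error. If partners are not closely matched, the leftover BMI difference passes straight into the estimated arm difference. Eligible BMI runs from above 30 to below 70 kg/m², so there is room for such differences. The protocol expects 16 bariatric subjects treated and 12 completing, about 6 per arm, so this comparison has little precision to spare.

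**Working it through.** **1. The plan's own sample size.** Item 3 gives 5 subjects (delta 2, SD 1.2), 6 subjects (delta 2.4, SD 1.5) and 8 per bariatric group after 20% dropout. A two-sided paired t-test at alpha 0.05 on pre/post change, reading the SD as that of the change, gives 79.3% power at n = 5 for the first and 87.5% at n = 6 for the second. Dropout: 6 / (1 − 0.20) = 7.5, rounded up to 8. The figures therefore reproduce as within-subject calculations. They contain no Ex vs SC comparison and take no credit for matching.

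**2. Standard error.** Let rho be the within-pair correlation of the tested quantity. The unpaired standard error exceeds the correct one by a factor of about 1/√(1 − rho):
- rho = 0: 1.00
- rho = 0.2: 1/√0.8 = 1.12
- rho = 0.3: 1/√0.7 = 1.20
- rho = 0.5: 1/√0.5 = 1.41

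For any positive rho the error is in the conservative direction.

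**3. Size with 6 pairs.** From the protocol: 12 completers, split equally by assumption. Further assumptions, since the protocol gives neither figure: an arm effect of 1.5 SD, and BMI explaining a share R² of the variance of the tested quantity. Partners lie within 0.2 SD of each other on BMI. Tests are two-sided at 0.05. Simulated results, to within about one point:

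| R² | Type I error, no BMI term | Power, no BMI term | Power, BMI covariate |
|---|---|---|---|
| 0 | 5% | 65% | 64% |
| 10% | 4% | 65% | 68% |
| 25% | 3% | 67% | 76% |
| 40% | 2% | 68% | 85% |

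If pairs are looser (mean BMI gap about 0.7 SD), type I error without the BMI term is about 4.5%, 3.6% and 2.5% at R² of 10%, 25% and 40%. The covariate then costs about 3 points of power when R² = 0.

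**4. Which row applies.** With one pre and one post value, the group x test interaction is a comparison of change between arms. A stable effect of BMI on the level of the outcome cancels; only BMI's relation to the change counts. The rows at 0 to 10% are the natural range there, a difference of −1 to +3 points. The 25% and 40% rows are plausible only for outcomes compared as levels. Omental depot composition is one: the pre-test biopsy is subcutaneous and optional, so omental tissue is available only at surgery.

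**5. Pair term instead of a covariate.** With 6 pairs, a pair term cuts the error degrees of freedom from 10 to 5, and the critical t rises from 2.228 to 2.571. Break-even on confidence-interval width is rho = 1 − (2.228/2.571)² ≈ 0.25. With 8 pairs it is 1 − (2.145/2.365)² ≈ 0.18. Dropout also breaks pairs: at 12 of 16 completing, and with independent dropout, 0.75² = 0.56 of 8 pairs, about 4.5, stay intact. Six complete pairs is the best case.

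**The case against.** The strongest reply is that the planned test is safe and may be no worse than a paired one. If BMI is unrelated to the tested outcome, the standard error is correct. If it is related, the test is conservative and adds no false positives through its standard error. Below a within-pair correlation of about 0.25, the unpaired test matches or beats a paired test at this size. All of that stands. It argues against a pair term as the main analysis, but not against a BMI covariate costing one degree of freedom, and it does not deal with BMI differences left within pairs.

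Two stronger readings are tempting. A reader might infer that power bought by matching has been thrown away. The sample-size section does not support this, because it sizes the arms on pre/post change only. A reader might also infer poor pairs from the timeline statement "Our team will interact with 4-5 subjects at one time". With batches of four and an assumed BMI SD of 7, the mean within-pair gap would be about 5 kg/m². But the protocol does not say that pairs are formed within those 4-5 subjects, nor that all of them are bariatric patients, and the SD is not given. A gap of that size (5/7 ≈ 0.7 SD) is also inconsistent with the close pairs assumed in the table.

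Operating time is a weak example of a level outcome, since the secondary outcome list plans to correlate it with other variables rather than compare it between arms.

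Finally, covariates are often left to an analysis plan. Here, however, the protocol itself states both the design and a model that leaves the matching out.

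**Conclusion.** The point holds as a mismatch between design and stated analysis. The unrandomised bariatric arms are built by match pairing and compared as if independent. The consequence depends on how strongly BMI relates to the tested outcome: none if unrelated; otherwise too large a standard error, a type I error below 5%, lost precision, and an arm difference that carries any remaining BMI imbalance. For change outcomes the likely power difference is about −1 to +3 points. Gains of about 9 points (67% to 76%) to 17 points (68% to 85%) need BMI to explain 25% to 40% of the variance, which is plausible only for level outcomes. These figures assume 6 close pairs and a 1.5 SD effect, neither of which comes from the protocol. It would go too far to say that the standard errors are wrong in every case, or that the stated power is compromised. The correction is cheap and worth making.

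**What to change.** In Statistical Considerations item 4, add baseline BMI as a covariate in the Ex vs SC models. In the repeated measures model it must enter with its interaction with test, because a BMI main effect alone leaves the group x test comparison of change unadjusted; equivalently, use BMI as a covariate for the change score. For outcomes measured only at surgery, add BMI directly. If BMI is left out, say why. Specify a pair-block analysis as a sensitivity check only, because with about 6 pairs it loses power unless the within-pair correlation exceeds about 0.25, and it drops subjects whose partner leaves. Name BMI as the matching variable in the study-design and statistical sections as well as in the abstract.

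Cost: one sentence and one degree of freedom per model, with no new data, since height and weight are measured at screening. If BMI proves unrelated to the outcome, about 1 point of power is lost with close pairs and about 3 with loose ones.
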